**STUDY SUMMARY/SYNPOSIS**

| **TITLE** | The EPOS Trial: Effective Patient-Clinician Communication in Community Mental Health Care |
| --- | --- |
| **SHORT TITLE** | The EPOS Trial |
| **Protocol Version Number and Date** | Version 2, Date 31/05/2012 |
| **Methodology** | Randomised control trial |
| **Study Duration** | 24 months |
| **Study Centre** | East London NHS Foundation Trust |
| **Objectives** | 1) To test whether regular use of the DIALOG+ intervention over a six month period improves patients' subjective quality of life.  2) To test whether DIALOG+ leads to improvements in recovery, objective social outcomes, social contacts, treatment satisfaction, the therapeutic relationship, needs, self-efficacy, psychopathological symptoms, and well being.  3) To test the cost-effectiveness of DIALOG+.  4) To investigate the extent to which clinicians adhere to the DIALOG+ manual, assess how it is implemented and explore the impact on the actual patient-clinician communication.  5) To gauge the experiences and opinions of clinicians and patients on the DIALOG+ intervention. |
| **Number of Patients** | 180. |
| **Main Inclusion Criteria** | Key workers  Professional qualification as a clinician (nurse, social worker, psychologist, occupational therapist, doctor);  More than 6 months experience of working in community mental health care;  Working as care coordinator.  Patients  Treatment in a community mental health care team in the NHS for at least one month;  No planned discharge for the next six months;  Clinical diagnosis of schizophrenia or a related disorder (F20-29);  Age between 18 and 65 years;  A mean score of lower than 5 on the MANSA;  Capacity to give informed consent. |
| **Method of Analysis** | Strict intention-to-treat or available case analysis |

**5.** **Analysis** **12**

**6.** **Publication Policy** **12**

**7.** **References** **12**

**1. Introduction**

**1.1 Background**

Approximately 1% of the population are affected by schizophrenia and related disorders with particularly high rates in urban areas (1). Such disorders result in significant distress for patients and carers and account for a substantial societal burden. They also generate high costs to the NHS through the need for ongoing intensive care and frequent hospitalisation, and to the society at large caused by loss of employment of patients and frequently also carers (2;3).

Patients with severe forms of schizophrenia are now regularly cared for in the community. As a result of major reforms of mental health care since the 1970s and substantial additional investments in the last 10 years, multi-disciplinary community mental health care teams have been set up throughout the UK and provide ongoing care. Every patient has a key worker (usually a nurse or social worker by background) who has regular meetings with the patient to assess their needs, engage them in treatment, discuss different treatment options and co-ordinate care. Yet, the interaction in these meetings is based more on common sense than on evidence based methods.

Whilst the evidence suggests that a more positive patient-clinician relationship is associated with more favourable outcomes (4-7), there is no evidence based intervention to achieve a better therapeutic relationship in community mental health care. Also, until recently there was no evidence based method to structure the communication between patient and clinician in a way that would eventually lead to more favourable clinical outcomes (8).

DIALOG is the first method to structure the patient-clinician interaction in community mental health care that has been shown to be associated with more favourable long term outcomes in a randomised controlled trial (9). In this computer-mediated intervention, patients are presented with fixed questions regarding their satisfaction with life and treatment and their needs for additional help. Subsequently, the ratings are displayed graphically and can be compared with ratings in previous meetings. In a cluster randomised controlled trial in six European countries, the DIALOG intervention was shown to be effective over a one year period. The intervention was associated with better subjective quality of life (SQOL), fewer unmet treatment needs and higher treatment satisfaction in patients with psychosis. The overall effect size was small. A stronger effect (medium effect size) was observed in the study site in the United Kingdom (East London) and in patients with more problematic baseline scores.

Following the trial, the National Institute for Health Research (NIHR) funded a programme to develop the intervention further both in terms of improving the technology and linking it with a simple psychological intervention informed by principles of Solution Focussed Therapy (SFT) and Cognitive Behavioural Therapy (CBT). The new intervention, combining the original intervention with a new 4-step approach to address problems raised by the patient, is called DIALOG+. The four steps consist of exploring the reasons for the dissatisfaction or wish for additional help and identifying positive coping skills; a forward looking consideration of best hopes and/or small changes; a discussion of all options for helpful actions by the patient, the clinician or other people; and an agreement of actions to be taken.

**1.2 Importance**

Patients diagnosed with schizophrenia or related disorders are the largest diagnostic group across all forms of secondary mental health services, and it can be estimated that more than 100,000 such patients are in care of community mental health care teams in England at any point of time (10). Established pharmacological and psychological treatments have only limited effect sizes in the long term treatment of schizophrenia, and are associated with substantial rates of non-adherence.

At present, patients regularly meet their key workers, but the patient-clinician interactions are not guided by evidenced based principles. A method to make these interactions more effective will not be a specialist programme for a small number of patients, but a generic method that can be utilised in routine care throughout the NHS. It does not require setting up new services or restructuring of organisations. It can be implemented at relatively low costs, particularly as it will not require extensive training of clinical staff, and can benefit tens of thousands of patients at the same time. Thus, even small health and social gains for individual patients will add up to substantial public health effects. This also applies to potential cost savings. The FOCUS study (in which patients’ outcomes were assessed by researchers and fed back to clinicians without structuring clinician-patient communication) suggested annual cost savings of regular outcome data feedback (which is also provided in DIALOG+) equivalent to £5172 per patient through reduced bed use (11). If replicated for only 20% of patients with schizophrenia and related disorders in community care in the NHS, the savings would exceed £100 million every year.

The procedure of DIALOG+ will also provide regular outcome data, i.e. patients’ ratings of satisfaction with life, treatment satisfaction and needs for further care. This data can be used to evaluate services on a local, regional and national level. So far, attempts to establish outcome assessment in routine community mental health care have largely failed, partly because it is difficult to motivate clinicians and patients to rate and enter outcome data on a regular basis. DIALOG+ provides a method to generate such data in way that is meaningful to clinicians and patients, and is likely to facilitate routine outcome assessment in secondary mental health services in the NHS.

**1.3 Rationale**

DIALOG+ differs considerably from the initial DIALOG intervention, warranting a new study. DIALOG+ involves a new version of the software (DIALOG 2.0) on a new platform (the iPad), further structures clinicians' behaviour according to the DIALOG+ manual, and involves training of clinicians. DIALOG+ aims to provide a way to deal with the specific concerns raised by the patient and, hence, equip the clinician as well as the patient with a method to explore and deal with problems.

Furthermore, we are seeking to conduct a more intensive intervention that will be delivered once a month over a six month period, rather than every two months over a one-year period, as in the original trial. We also wish to include a wider range of patients, as opposed to patients with persistent disorders who had been in care for an average of 15 years in the previous study. Finally, we wish to compare the intervention with a more defined control condition than treatment as usual, which will help to control for the effect of the implementation of an electronic device in the clinical setting and assessment of satisfaction, without providing feedback to the meeting, expanding on problematic domains or exploring needs for additional help. All these differences justify a new trial testing the effectiveness of DIALOG+.

**2. Study objectives and design**

**2.1 Study objectives**

1) To test whether the regular use of the DIALOG+ intervention over a six month period improves patients’ subjective quality of life.

2) To test whether DIALOG+ leads to patient improvements in recovery, objective social outcomes, social contacts, treatment satisfaction, the therapeutic relationship, needs, self-efficacy, psychopathological symptoms, and well being.

3) To test the cost-effectiveness of DIALOG+.

4) To investigate the extent to which clinicians adhere to the DIALOG+ manual, assess how it is implemented and explore the impact on the actual patient-clinician interaction.

5) To gauge the experiences and opinions of clinicians and patients on the DIALOG+ intervention.

**2.2 Study design**

An exploratory pragmatic cluster randomised controlled trial on the effectiveness and cost-effectiveness of DIALOG+. There is an additional qualitative component involving videotaping of patient-clinician dyads, and focus groups with patients and key workers.

Intervention to be tested

In the experimental group, DIALOG+ will be used as defined in the accompanying manual, and the DIALOG 2.0 software will run on an Apple iPad tablet. All clinicians in the experimental group will be trained in two sessions before the beginning of the intervention and receive a further two sessions for support and advice after about two months. Clinicians will be instructed to use DIALOG+ at least once per month over a six month period, although this is likely to vary due to the practical organisation of care. Clinicians and patients in the experimental group may decide to continue with DIALOG+ after the end of the six month intervention group. This will be documented and considered in the analysis of outcomes after the follow-up period.

Control condition

The control condition will include treatment as usual plus a defined intervention that also involves the use of an Apple iPad tablet and an assessment of the patient’s satisfaction. The patient will use the device to rate his/her satisfaction on the 11 domains of the DIALOG scale. The instruction will be to undertake such assessments after a meeting once per month and not to inform the clinician about the rating. This will help to control for the effect of the implementation of an electronic device in the clinical setting and assessment of satisfaction without providing feedback to the meeting, expanding on problematic domains or exploring needs for additional help.

Allocation to condition

Clinicians will be recruited from CMHTs in East London NHS Foundation Trust. Once clinicians have been recruited, patients meeting the eligibility criteria will be identified on their caseloads and randomly selected for participation in the study. Patients will then be asked by the clinicians for consent to be approached by a researcher. If patients consent, a researcher will contact them, do the baseline assessment and check all inclusion criteria. Due to ceiling/floor effects, patients who score very favourably on the primary outcome at baseline render a substantial improvement unlikely if not impossible. Therefore, patients who rate their mean subjective quality of life on the Manchester Short Assessment of Quality of Life (MANSA) (12) as 5 (satisfied) or higher will be excluded. Once five patients (per clinician) meeting the inclusion criteria have been recruited, the clinician – and correspondingly, his/her patients – will be randomly allocated to either the intervention or control group. Clustering of clinicians will prevent contamination effects in the study. Randomisation will be done by an independent statistician at the Pragmatic Clinical Trials Unit (PCTU) through e-mail.

Outcomes

Outcomes will be assessed at baseline and after 3, 6, and 12 months. We will attempt to keep the researchers assessing the outcomes masked about the allocation of the patients. If masking of the interviewer cannot be maintained, we will put researchers working at the Unit for Social and Community Psychiatry at the Newham Centre for Mental Health who are independent of the core research team)into contact with patients via telephone for conducting the assessment of the primary outcome and, as far as feasible, secondary outcomes. In such cases, patients will be asked not to discuss the treatment they received for the duration of the call.

The primary outcome will be subjective quality of life, measured on the MANSA (as in the original trial).

Secondary outcomes for the trial will consist of:

- Recovery as measured on the severity parts of each of the 24 items of the CHOICE scale(13) (satisfaction, i.e. the second part of each item, is already assessed on the MANSA)
- Objective Social Outcomes (SIX) (14), also assessed using the MANSA (sections 2 and 3), at 6 and 12 months only
- Social contacts in the last week in a structured interview
- Treatment Satisfaction on the Client Satisfaction Questionnaire (CSQ-8) (15)
- The Therapeutic Relationship on the Scale for Assessing Therapeutic Relationships in community mental health care (patient and clinician versions) (16)
- Needs on the Camberwell Assessment of Need Short Appraisal Schedule, patient-rated version(17)
- Self-Efficacy on the General Self-Efficacy Scale (18)
- Psychopathological Symptoms on the Brief Psychiatric Rating Scale (19)
- Costs of formal and informal care, assessed on the Client Service Receipt Inventory(20)
- Mental well-being on the Warwick-Edinburgh Mental Well-Being Scale (WEMWBS) (21).

Qualitative Assessments

For assessing the feasibility of the intervention, adherence to the manual and its effects in the patient-clinician meetings, each patient-clinician pair in the intervention group will have one of their meetings video-taped (or when unpractical audio-taped) and analysed. In the control group, we will do the same for 20% of the sample. Adherence to manual in the intervention group will be assessed against the manual for DIALOG+.

The software will automatically record what domains were explicitly discussed in DIALOG+ and what actions were agreed.

At the end of the intervention, separate focus groups will be conducted with patients and clinicians in the intervention group to obtain their experiences and suggestions for improvements.

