**3.2 Number of subjects**

We will recruit 36 key workers and 180 patients, with 18 key workers and 90 patients in each of the conditions (five patients per key worker). Given the likely drop out of clinicians due to job changes or personal moves, we anticipate the loss of six key workers and 30 of their patients. With a patient drop out rate of less than 10% of the remaining 150 patients (as in the original trial it was less than 10% over a one year period) we will end with a sample of 136 patients. Assuming a practically negligible cluster effect (as in the original trial) the sample size will be sufficient to detect a medium effect size of 0.5 (Cohen’s D) with 80% power at the 5% significance level. A slightly higher effect of 0.57 will be detected with 90% power. The effect size of 0.5 would require that at the end of the intervention patients in the experimental group rate their satisfaction with at least 3 out of 12 life domains in the MANSAat least one point higher than patients in the control group. The sample size will also be sufficient to provide the required variation of experiences for addressing all other research questions.

Out of the caseload of all potentially eligible patients, we will randomly select 7 patients (allowing for 2 patients not fulfilling the inclusion criteria or not consenting to participate) per key worker. The remaining patients on the caseload of each key worker will be randomly ranked. They will be approached one-by-one if and when there is a need to recruit more patients for the given worker (e.g. in case more than 2 of the originally selected 7 do not consent to participate). Once all patients for one key worker have been recruited, the key worker will be randomly allocated to the intervention or control condition and receive either the training for DIALOG+ or the instructions for the control condition.

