**3.3 Inclusion criteria**

To reflect the pragmatic nature of the trial, there will be wide inclusion criteria and very few exclusion criteria for both clinicians and patients. The inclusion criteria for patients will be wider than in the original DIALOG trial to test whether patients with more acute disorders, who have not been in care for many years and whose treatment in secondary services may not continue for another year, can also be recruited.

Patients

- Treatment in a community mental health care team in the NHS for at least one month;
- No planned discharge for the next six months;
- Clinical diagnosis of schizophrenia or a related disorder (F20-29);
- Age between 18 and 65 years; A mean score of lower than 5 on the MANSA;
- Capacity to give informed consent.

Key workers

- Professional qualification as a clinician (nurse, social worker, psychologist, occupational therapist, doctor);
- More than 6 months experience of working in community mental health care;
- Working as care coordinator.

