**5. Analysis**

Quantitative data will be analysed descriptively and by comparing outcomes in the two groups. Our primary analysis will be a strict intention-to-treat analysis or an available case analysis following intention-to-treat principles. Which analysis is used will depend on the number of missing values, the validity of any necessary assumptions (which may be particularly uncertain in this case) and the ease of multiple imputation (which will be used for the intention-to-treat analysis) given the analysis model. Currently, multiple imputation is, for example, much less straightforward if we opt for generalised estimating equations as our model of analysis. A decision about strict intention-to-treat or available case analysis will be made and written into a full analysis plan before any analysis is undertaken and before data are unblinded.

We intend to use generalised linear models as appropriate to the outcome, with fixed effects for the intervention and random effects for clinician (to adjust for the cluster effect of several patients treated by the same clinician). At end of treatment we expect missing data to be minimal. We will use sensitivity analyses to explore the impact of missing data.

Videotapes will be analysed according to specific criteria for adherence to manual. Audiotapes from focus groups will be analysed using thematic analysis.

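### Read literally, the schedule for objective social outcomes (SIX) has no baseline measurement; the protocol should say whether SIX is collected at baseline and use that value in the SIX comparison

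*Protocol*

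**What the plan says.** Under Outcomes in Protocol section 2.2, one schedule is set for everything: "Outcomes will be assessed at baseline and after 3, 6, and 12 months". In the list of secondary outcomes that follows, SIX alone carries a timing restriction: "also assessed using the MANSA (sections 2 and 3), at 6 and 12 months only". No other section mentions a baseline SIX.

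Three other places bear on the point.

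- **Section 2.1, objective 2** includes SIX among the outcomes to be tested: "To test whether DIALOG+ leads to patient improvements in recovery, objective social outcomes, social contacts".
- **Section 2.2, Allocation to condition**, has a researcher "do the baseline assessment and check all inclusion criteria" before the clinician is randomised. The MANSA is in use at that stage, because section 3.3 requires "A mean score of lower than 5 on the MANSA".
- **Section 5** describes the analysis model as one "with fixed effects for the intervention and random effects for clinician". It names no baseline covariate or change score for any outcome, and it refers to a full analysis plan still to be written.

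**The concern.** Set against a four-point schedule stated shortly before, a restriction to two of those points excludes the other two, baseline as well as 3 months. Leaving out the 3-month visit is easy to understand for social circumstances that may move slowly. No reason is given for leaving out baseline, and the omission is odd because SIX is drawn from an instrument that is already in use at that interview.

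If field staff follow the literal text, three things are lost for SIX:

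- the arms cannot be shown to be comparable on it at baseline;
- change within patients cannot be described;
- the follow-up comparison cannot be adjusted for its own starting value.

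Clinicians are randomised, 18 per arm, so a chance difference in their patients' social circumstances is quite possible. A baseline value would reveal it and allow adjustment. A baseline that is not collected cannot be supplied later by an analysis plan, so the collection schedule has to be right in the Protocol.

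**Working it through.** **Step 1. The texts side by side.**

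| Place in Protocol | Baseline | 3 months | 6 months | 12 months |
|---|---|---|---|---|
| 2.2, general schedule | yes | yes | yes | yes |
| 2.2, SIX, literal reading | no | no | yes | yes |
| 2.2, SIX, if the restriction concerns follow-up visits only | yes | no | yes | yes |

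The text does not settle which of the last two rows is meant. Sections 2.2 and 3.3 establish that the MANSA mean score is obtained at baseline. They do not mention sections 2 and 3 of the instrument there.

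**Step 2. The plan's own power figure.** The Protocol gives no power figure for SIX. Its figures in section 3.2 concern the sample size as a whole and are argued from the MANSA. They are reproduced here only to fix the sample on which SIX would be analysed. Inputs from section 3.2:

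- "We will recruit 36 key workers and 180 patients, with 18 key workers and 90 patients in each of the conditions";
- after losses, "we will end with a sample of 136 patients", taken here as 68 per arm;
- a cluster effect treated as negligible;
- 5% significance, assumed two-sided.

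Power = Φ(d / √(2/68) − 1.96), with √(2/68) = 0.1715.

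- d = 0.5: 83.0% (82.5% with the t distribution), against a stated 80%. The sample is sufficient, as claimed.
- d = 0.57: 91.4% (91.0% with the t distribution), against a stated 90%.

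The stated figures hold, and nothing in this point changes them.

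**Step 3. What a baseline SIX would add (illustrative).** Let r be the correlation between SIX at baseline and at follow-up. The Protocol gives no value, so 0.5 to 0.8 is an assumption. SIX is treated as a continuous score in a linear model, with negligible clustering.

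- Residual variance after adjustment, as a fraction of the unadjusted variance: 1 − r².
- Equivalent multiple of patients: 1 / (1 − r²).
- Difference detectable with 80% power, in SD units: (1.96 + 0.84) × √(1 − r²) × √(2/68).

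| Analysis | 1 − r² | Equivalent multiple of patients | Detectable difference | Power at 0.5 SD |
|---|---|---|---|---|
| Follow-up values only | 1 | 1 | 0.48 SD | 83% |
| Adjusted, r = 0.5 | 0.75 | 1.33 | 0.42 SD | 92% |
| Adjusted, r = 0.7 | 0.51 | 1.96 | 0.34 SD | 98% |
| Adjusted, r = 0.8 | 0.36 | 2.78 | 0.29 SD | over 99% |

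**Step 4. Adjustment or change score.** For a change score the factor √(1 − r²) becomes √(2(1 − r)). The detectable difference is then 0.48 SD at r = 0.5, no better than using follow-up values alone, and 0.30 SD at r = 0.8. Over this range the gain is larger if the baseline enters as a covariate.

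**The case against.** The strongest reply is that nothing is missing. After a sentence that lists baseline and three follow-ups, a limit to 6 and 12 months can naturally be read as a limit on the follow-ups, with baseline taken for granted. That reading is reasonable and may be what was meant. It does not remove the point, because the text allows both readings and the literal one loses data for good.

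A reader might infer that without a baseline the trial cannot test objective 2 for SIX. The Protocol does not support that. Section 5 compares randomised groups, and a between-arm comparison at 6 and 12 months is a valid test of the effect of DIALOG+ without any baseline value.

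A reader might also infer that a difference at follow-up could not be told apart from chance imbalance between clinicians. That too goes too far. The standard error, with the clinician random effect in section 5, already allows for such imbalance. What is lost is precision and sight of the imbalance.

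Nor can it be said that SIX is already collected at baseline. Only the mean MANSA score is documented there.

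Finally, the choice of covariates may properly be left to the analysis plan, so the silence of section 5 is no defect. That stands: the point against the Protocol is the collection schedule. SIX is also one of several secondary outcomes in a trial that describes itself as exploratory.

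**Conclusion.** The point holds as a minor one. The SIX entry in section 2.2 does not agree with the general schedule in the same section. Taken at its word, it leaves this single outcome without a baseline. The Protocol does not resolve whether that is intended.

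The consequence is a less precise SIX comparison, with no view of baseline comparability or of change within patients. The comparison itself remains valid. The size is a 25% to 64% reduction in residual variance forgone, so a detectable difference of 0.48 SD where 0.29 to 0.42 SD might be had. These figures rest on the assumed correlation, a continuous score, negligible clustering and 68 patients per arm. They are illustrations, since the Protocol makes no claim of power for SIX. If sections 2 and 3 are in practice completed at baseline, no data are lost and only the wording needs correcting.

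**What to change.** - In section 2.2, reword the timing of SIX to: at baseline, 6 and 12 months (not at 3 months).
- State that MANSA sections 2 and 3 are completed at the baseline interview, where the MANSA is already used for eligibility.
- In the analysis of SIX, include the baseline value as a covariate. This can be written in the analysis plan.

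The cost is one phrase in the Protocol and at most a few extra minutes at an interview that already takes place, or none if those sections are already completed then. The primary outcome, eligibility criteria and sample size do not change.
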